**Fig. 1 Fig1:**
[figure not shown]
Flow of participants

### Outcome measures

The primary outcome measures for this study is weight loss, body composition and waist circumference. Secondary outcome measures include blood glucose, insulin and lipids, blood pressure, arterial stiffness and hip circumference, as indicators of changes to cardiometabolic disease risk factors. Dietary and physical activity compliance, eating behaviour, quality of life, mental well-being (stress, anxiety, and depression), self-control, self-efficacy, Facebook activity, and program evaluation will also be evaluated as further secondary outcome measures. These clinical and self-reported measurements have been chosen to test the participants’ adherence to the weight management program, and to compare the outcomes of the two different weight loss program delivery methods.

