### Summary of intervention

One hundred and twenty overweight and obese participants from the Perth community will be enrolled into the study, and randomly divided into three groups: two intervention groups and a control group. The two intervention groups will be instructed to follow the CSIRO TWD [17] weight management program for the twelve-week intervention period. One of the intervention groups will receive the diet via the social networking website Facebook and will be enrolled into a support network which is hosted via the Facebook site. The other group will receive the intervention in written form (pamphlet) alone. Both of the intervention groups will be supplied with pedometers (G Sensor 2025 Accelerometer, Walk with Attitude Australia) and set a target of 10,000 steps per day. The control group will follow the Australian Dietary Guidelines [39] as well as National Physical Activity Guidelines for Adults [16] as usual care. Participants will complete a series of questionnaires which will evaluate key psychological variables (see below) and attend Curtin University for assessment of body weight and other clinical outcome variables (outlined in the Design/Methods section) at weeks 0, 6, and 12 and at further 12-week follow-up (week24). The primary outcome measures in this trial include weight, body composition and waist circumference. Blood glucose, insulin, blood pressure, arterial stiffness [40], physical activity, eating behaviour, mental well-being (stress, anxiety, and depression), social support, self-control, self-efficacy, Facebook activity, and program evaluation are secondary outcome measures. Changes in psychological and clinical outcomes are expected to be greatest in the intervention group delivered and supported by social media relative to the pamphlet intervention and control groups. It is anticipated that social media will provide an invaluable resource for health professionals, serving as a low maintenance vehicle for communicating with patients and a source of social support and information sharing for individuals undergoing lifestyle modifications.

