### Study design

This will be a three-armed, randomised, controlled, parallel design intervention study undertaken over a 12 week period, with a subsequent 12 week follow-up. Interested participants will be screened according to the inclusion/exclusion criteria and those eligible will be allocated a number, stratified according to age and gender, and then randomly allocated to one of the three groups of 40 participants, using dedicated computer randomisation software [41, 42] The allocated number will also be used as the participants’ identification number, to be used on all records and questionnaires. The three groups will consist of: the Control Group who will follow the Australian dietary guidelines [39] and National Physical Activity Guidelines for Adults [16], the Pamphlet Group who will be instructed in the weight management program by written information, and the social media group who will receive exactly the same weight management program via Facebook in the Facebook Group. [Please see Fig. 1: Flow of participants.] The initial twelve-week weight management program will be presented to the two intervention groups as a condensed version of the CSIRO TWD [17], which includes information of the weight management program, along with weekly checklists available from the CSIRO TWD [43]. Before the commencement of the trial, participants will attend an information session specific to their group allocation, where the participation requirements, including questionnaires and outcome measurements, will be explained. An additional file explains this in greater detail [please see Additional file 1]. During the Facebook Group information session, participants will be provided with additional information about using Facebook in this context. Facebook Group participants will also be made aware of the role of the primary investigator as administrator and facilitator of the Facebook Group. In addition, participants in this group will be informed that at the completion of the twelve-week intervention period, all facilitation will cease, however the group will still be monitored by the facilitator to ensure that they continue to conduct themselves according the instructions provided. This change in strategy for the twelve-week follow-up period will be used to determine whether the Facebook Group has become self-sustaining. An additional file explains the added information provided for Facebook Group participants in greater detail [please see Additional file 2].

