### Assessments

All participants will be required to attend regular clinical appointments for a duration of approximately 15 min, as follows: at baseline, at weeks 6 and 12, and then again for a follow-up appointment at week 24. Prior to each appointment, participants will complete a Three-Day Food Record and selection of questionnaires to monitor compliance and address some of the secondary outcome measures. The Bouchard Three-Day Physical Activity Record [44] will be used to measure of total physical activity. The Three-Factor Eating Questionnaire (TFEQ) [45] will provide a measure of dietary restraint, disinhibition and hunger, and will also be used here to assess changes in satiety. The Self-Efficacy Scale [46] will be used to assess changes to participants’ self-efficacy. The WHO Quality of Life Questionnaire [47] will be used to determine changes in participants’ quality of life. The short version of the Depression Anxiety Stress Scale (DASS 21) [48] will be used to measure changes in general psychological wellbeing. The Self-Control (Brief) Scale [49] will be used to provide an understanding of participants’ impulse control as it relates to eating behaviour. The Diet and Physical Activity Survey, constructed using the Theory of Planned Behaviour [50], will be used to determine participants’ intentions with regard to the dietary and physical activity guidelines being used in the trial. The Survey of Weight Management Program has some general questions regarding the ease of use of the dietary and physical activity guidelines being utilized; there will be an extra section for Facebook Group participants to assess the preferred device for accessing the weight management information provided on Facebook. For Facebook Group participants only, the Social Media Survey will be used to assess participants’ attitudes to social media. The final questionnaire will also be administered to Facebook Group participants only; the Facebook Intensity and Network Density Scales contains a combination of questions used in previous social media research [51, 52]. It will be adapted for this study to assess the degree to which participants make use of Facebook, as well as the strength and frequency of the social interactions within the Facebook Group. In addition, the Facebook Group page will be printed at the end of each week to corroborate self-reported Facebook usage data and monitor participants’ online behaviour. Participants will be given questionnaires (including the Food Record and Physical Activity Record) at each clinic appointment, according to their group allocation. [For further information regarding the assessments please see Table 1: Schedule of Assessments.] Participants will be instructed to use their participant identification number only when completing all documents relating to this trial [42].

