### Statistical analysis

Based on a three group study with repeated measures, a sample size of 96 achieves 80 % statistical power to detect a medium to large effect size (Cohen’s *d* = 0.4); that is, a difference of 6 kg between the two intervention groups, with alpha set at 0.05. To allow for an attrition rate of 20 %, a total of 120 participants will be recruited; i.e. 40 participants per group. Stratified randomisation will be used to ensure that each group is matched in age and gender. The results will be analysed using a mixed repeated measures analysis of variance (ANOVA) design. Data will be expressed as mean (±SEM) and assessed for normality to ensure that the assumptions of the analysis are met. If significant between groups effects are present, post hoc analysis will be conducted using the Least Significant Difference (LSD) method. Statistical significance will be considered at p < 0.05. All statistical analyses will be performed using SPSS 21.0 for Windows (SPSS Inc., Chicago, IL), and conducted using the participant identification number only [42].

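### Three unranked primary outcomes are each tested at p < 0.05, so the chance of at least one false primary claim is about 8% to 14% if any one of them can carry the claim

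*Protocol article*

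**What the plan says.** The primary outcomes are stated twice in the body of the article, with the same three members and no ranking:

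- Summary of intervention: "The primary outcome measures in this trial include weight, body composition and waist circumference".
- Outcome measures: "The primary outcome measures for this study is weight loss, body composition and waist circumference".

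The Statistical analysis section then sets the testing rule:

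- Model: "The results will be analysed using a mixed repeated measures analysis of variance (ANOVA) design".
- Post hoc step: "If significant between groups effects are present, post hoc analysis will be conducted using the Least Significant Difference (LSD) method".
- Threshold: "Statistical significance will be considered at p < 0.05".

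The sample-size statement in that section, "with alpha set at 0.05", is built on weight only: a 6 kg difference between the two intervention groups. Participants are "randomly allocated to one of the three groups of 40 participants" and measured "at baseline, at weeks 6 and 12, and then again for a follow-up appointment at week 24". The Hypotheses section ties its weight-loss figures (about 2 kg and about 8 kg) to the twelve-week intervention, but no section labels week 12 as the primary time point.

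**The concern.** Each primary outcome gets its own test at the full 5%. Nothing ranks the outcomes, splits the 5% between them, or says how many must succeed. If one success is enough, the error rate for the trial's main conclusion exceeds the 5% that the plan states.

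The practical risk is a trial that misses on weight, the outcome it was sized for, and still reports a positive primary result on waist or body composition. With no order fixed, the outcome that carries the conclusion could be chosen after the data are seen.

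**Working it through.** **Inputs from the article**

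- Primary outcomes: 3, unranked (Summary of intervention; Outcome measures).
- Significance level: 0.05 for every test, no correction across outcomes (Statistical analysis).
- Groups: 3, with 96 evaluable participants in all, so 96/3 = 32 per group (Statistical analysis).
- Visits: weeks 0, 6, 12 and 24, entered in one mixed ANOVA per outcome.
- LSD only after a significant between-groups effect.

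**Inputs assumed, because the article gives none**

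- Between-outcome correlation: varied from 0 to 0.95.
- Within-person correlation over visits: 0.8, equal for all pairs of visits.
- Body composition counted as one variable.

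**Step 1. The plan's own figure.** The article states no familywise error rate. Its recruitment figure does reproduce: 96/(1 − 0.20) = 120. The 96 itself can be neither confirmed nor refuted from the stated inputs. It matters here only because it rests on weight.

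**Step 2. Independent outcomes.** P(at least one false claim) = 1 − (1 − 0.05)^3 = 1 − 0.857 = 0.143, which is 2.9 times 5%.

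**Step 3. Correlated outcomes.** The planned mixed ANOVA was simulated with no true differences anywhere: 3 groups of 32, 4 visits, 3 outcomes, 20,000 runs per setting. The Monte Carlo standard error near 10% is √(0.10 × 0.90/20,000) ≈ 0.2 percentage points.

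| Between-outcome correlation | Group effect: any of 3 false | Ratio to 5% | Group-by-time effect: any of 3 false |
|---|---|---|---|
| 0 | 14.1% | 2.8 | 14.1% |
| 0.5 | 12.4% | 2.5 | 13.0% |
| 0.7 | 11.4% | 2.3 | 11.5% |
| 0.8 | 10.3% | 2.1 | 10.5% |
| 0.9 | 8.3% | 1.7 | 8.7% |
| 0.95 | 7.5% | 1.5 | 7.5% |

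A separate simulation with 32 per group gave 14.3%, 11.1%, 8.6% and 7.8% at correlations 0, 0.7, 0.9 and 0.95. The size is nearly the same whichever of the two effects is decisive, provided only one is.

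**Step 4. Does LSD add to this?** With the between-groups gate, the chance of a false claim per outcome was 4.8% to 5.3%, identical to the F test alone, and the figures over three outcomes were unchanged. Without the gate it would have been about 12% per outcome, but the article does state the gate.

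**Step 5. What correction by splitting alpha would cost.** Per-outcome level: 0.05/3 = 0.0167. For a design with 80% power at two-sided 0.05, power becomes Φ(1.960 + 0.842 − 2.394) = Φ(0.408) ≈ 66%. Keeping 80% multiplies the sample by ((2.394 + 0.842)/(1.960 + 0.842))² = (3.236/2.802)² ≈ 1.33. That takes 96 to about 129 evaluable, and 129/0.8 = 161.25, so about 162 recruited for equal groups.

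**The case against.** **No decision rule is stated.** The Abstract calls the three measures initial indicators of adherence, which can be read as joint evidence on one construct. If all three had to succeed, there would be no inflation. This stands as a condition: the figures apply only if one success suffices. The article states neither rule, and leaving that open is part of the problem.

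**An article may leave multiplicity to a fuller document.** That is fair for the choice of body-composition variable and for detailed testing procedures, and their absence is not counted here. The choice of primary outcomes and the 0.05 threshold are not deferred, however. The article fixes both.

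**Week 12 and weight are already implied.** This largely stands. The hypotheses point to week 12, the later period is described as follow-up with its own question, and the sample size uses weight. It makes the remedy easy, but it does not rank the three outcomes.

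**Stronger readings that a reader might infer.**

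- *LSD is unadjusted, so it inflates the error.* LSD is used only after a significant between-groups effect. With three groups, that holds about 5% per outcome when no group differs.
- *Four visits mean four sets of tests.* Visits are levels of one ANOVA per outcome, and week 0 is baseline. Ungated testing of every pair at every post-baseline visit would give 39% to 64% over three outcomes, but the article plans no such testing.
- *Either the group or the group-by-time effect may count.* That would give 14% to 26%. The article does not say that either suffices.
- *The error is always double to triple 5%.* It falls to 1.5 to 1.7 times at correlations of 0.9 to 0.95.

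**Conclusion.** The concern holds for the three co-listed primary outcomes and for nothing wider. If any one of them can support a primary claim, the chance of at least one false primary claim is about 8% to 14% rather than 5%. It is above 5% at every correlation tried, from 0 to 0.95. The size rests on the unstated correlation, on body composition being a single variable, and on the simulation's assumed within-person correlation. More than one body-composition variable would raise it. This should be fixed, but it does not undermine the design: weight and week 12 already stand out as the natural lead.

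**What to change.** Amend Summary of intervention, Outcome measures and Statistical analysis together:

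1. Name one primary endpoint: change in body weight from baseline to week 12, Facebook versus Pamphlet, tested at 0.05. This matches the sample-size statement and the hypotheses.
2. Make waist circumference and one named body-composition variable key secondary outcomes, tested after weight in fixed order or by Holm.
3. Treat weeks 6 and 24 as supportive.

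This restores the 5% level for the primary claim and needs only a change of wording. The cost is that waist and body composition can no longer carry a primary claim alone. If the investigators want all three to keep that status, splitting alpha at 0.0167 each caps the total at 5%. The price is power of about 66% instead of 80%, or about 162 recruited instead of 120.

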### Assessments

All participants will be required to attend regular clinical appointments for a duration of approximately 15 min, as follows: at baseline, at weeks 6 and 12, and then again for a follow-up appointment at week 24. Prior to each appointment, participants will complete a Three-Day Food Record and selection of questionnaires to monitor compliance and address some of the secondary outcome measures. The Bouchard Three-Day Physical Activity Record [44] will be used to measure of total physical activity. The Three-Factor Eating Questionnaire (TFEQ) [45] will provide a measure of dietary restraint, disinhibition and hunger, and will also be used here to assess changes in satiety. The Self-Efficacy Scale [46] will be used to assess changes to participants’ self-efficacy. The WHO Quality of Life Questionnaire [47] will be used to determine changes in participants’ quality of life. The short version of the Depression Anxiety Stress Scale (DASS 21) [48] will be used to measure changes in general psychological wellbeing. The Self-Control (Brief) Scale [49] will be used to provide an understanding of participants’ impulse control as it relates to eating behaviour. The Diet and Physical Activity Survey, constructed using the Theory of Planned Behaviour [50], will be used to determine participants’ intentions with regard to the dietary and physical activity guidelines being used in the trial. The Survey of Weight Management Program has some general questions regarding the ease of use of the dietary and physical activity guidelines being utilized; there will be an extra section for Facebook Group participants to assess the preferred device for accessing the weight management information provided on Facebook. For Facebook Group participants only, the Social Media Survey will be used to assess participants’ attitudes to social media. The final questionnaire will also be administered to Facebook Group participants only; the Facebook Intensity and Network Density Scales contains a combination of questions used in previous social media research [51, 52]. It will be adapted for this study to assess the degree to which participants make use of Facebook, as well as the strength and frequency of the social interactions within the Facebook Group. In addition, the Facebook Group page will be printed at the end of each week to corroborate self-reported Facebook usage data and monitor participants’ online behaviour. Participants will be given questionnaires (including the Food Record and Physical Activity Record) at each clinic appointment, according to their group allocation. [For further information regarding the assessments please see Table 1: Schedule of Assessments.] Participants will be instructed to use their participant identification number only when completing all documents relating to this trial [42].

**Table 1 Tab1:** Schedule of assessments

Measurement by Group	Week 0			Week 6			Week 12			Week 24		
	CG	PG	FG	CG	PG	FG	CG	PG	FG	CG	PG	FG
3-Day Food Record	•	•	•	•	•	•	•	•	•	•	•	•
Physical Activity Record	•	•	•	•	•	•	•	•	•	•	•	•
Three Factor Eating Questionnaire	•	•	•	•	•	•	•	•	•	•	•	•
Self-Efficacy Scale	•	•	•	•	•	•	•	•	•	•	•	•
WHO Quality of Life	•	•	•	•	•	•	•	•	•	•	•	•
Depression Anxiety Stress Scale	•	•	•	•	•	•	•	•	•	•	•	•
Self-Control (Brief) Scale	•	•	•	•	•	•	•	•	•	•	•	•
Diet & Physical Activity Survey	•	•	•	•	•	•	•	•	•	•	•	•
Survey of Weight Management Program*				•	•	•	•	•	•			
Social Media Survey			•			•			•			•
Facebook intensity & Network Density Scales						•			•			•
Height	•	•	•									
Weight	•	•	•	•	•	•	•	•	•	•	•	•
Blood pressure	•	•	•	•	•	•	•	•	•	•	•	•
Arterial stiffness	•	•	•	•	•	•	•	•	•	•	•	•
Blood glucose	•	•	•	•	•	•	•	•	•	•	•	•
Waist circumference	•	•	•	•	•	•	•	•	•	•	•	•
Hip circumference	•	•	•	•	•	•	•	•	•	•	•	•
Body Composition	•	•	•	•	•	•	•	•	•	•	•	•
Blood lipids	•	•	•				•	•	•			
Blood insulin	•	•	•				•	•	•			

Key: CG = Control Group; PG = Pamphlet Group; FG = Facebook Group

* There will be two versions of the Survey of Weight Management Program. Version 2 will include an additional section specific to Facebook Group participants only

At each clinical appointment, weight will be recorded in light clothing without shoes. (UM-018 Digital Scales; Tanita Corporation, Tokyo, Japan). Body composition will be measured by bioelectrical impedance analysis (BIA) in light clothing without shoes using the digital scales just mentioned. Height will be measured without shoes to the nearest 0.1 cm using a wall-mounted stadiometer (26SM 200 cm SECA, Hamburg, Germany). Height and weight measurements will be used to calculate participants’ BMI. Waist circumference will be measured in the standing position at the narrowest area between the lateral lower rib and the iliac crest; hip circumference will be measured at the widest area across the buttocks. Briefly, fasting blood glucose will be taken using the Accu-Chek® Performa glucometer and lancing device (Roche, Australia). Blood pressure will be assessed with an automated, calibrated sphygmomanometer (Dinamap, Compact T, Critikon, Germany). Pulse contour analysis (PCA) will be used to assess arterial stiffness using the Pulse Trace PCA 2 (CareFusion, NSW, Australia). In addition, at weeks 0 and 12 participants will be required to attend a local pathology collection centre (PathWest Laboratory Medicine, Western Australia) for blood tests to measure lipids (triglycerides (TG), total cholesterol (TC), low density lipoprotein (LDL) and high density lipoprotein (HDL)) and insulin. [For further information regarding the assessments please see Table 1: Schedule of Assessments.]

### Statistical analysis

Based on a three group study with repeated measures, a sample size of 96 achieves 80 % statistical power to detect a medium to large effect size (Cohen’s *d* = 0.4); that is, a difference of 6 kg between the two intervention groups, with alpha set at 0.05. To allow for an attrition rate of 20 %, a total of 120 participants will be recruited; i.e. 40 participants per group. Stratified randomisation will be used to ensure that each group is matched in age and gender. The results will be analysed using a mixed repeated measures analysis of variance (ANOVA) design. Data will be expressed as mean (±SEM) and assessed for normality to ensure that the assumptions of the analysis are met. If significant between groups effects are present, post hoc analysis will be conducted using the Least Significant Difference (LSD) method. Statistical significance will be considered at p < 0.05. All statistical analyses will be performed using SPSS 21.0 for Windows (SPSS Inc., Chicago, IL), and conducted using the participant identification number only [42].

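### Allocation is stratified by age and gender, but the analysis model as described names neither factor, so its between-arm tests would be somewhat conservative

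*Protocol article*

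**What the plan says.** Two places in the Protocol article describe the allocation. Study design says that eligible participants are "stratified according to age and gender, and then randomly allocated to one of the three groups of 40 participants". Statistical analysis repeats the intention: "Stratified randomisation will be used to ensure that each group is matched in age and gender". Neither gives the number of age bands, their cut-points or a block size.

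The next sentence of Statistical analysis names the model: "The results will be analysed using a mixed repeated measures analysis of variance (ANOVA) design". Pairwise comparisons are conditional: "If significant between groups effects are present, post hoc analysis will be conducted using the Least Significant Difference (LSD) method". Age, gender and stratum are not listed as factors or covariates anywhere in the article. Nothing says that they will be left out either.

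The outcomes concerned are set out in Summary of intervention: "The primary outcome measures in this trial include weight, body composition and waist circumference". They are measured at weeks 0, 6, 12 and 24.

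**The concern.** Stratified allocation makes the arms alike in age and gender, so those factors contribute little or nothing to chance differences between arms. A model that omits them still counts the variance they explain as error. The reported standard error then exceeds the true one, and the precision that stratification could give is not used.

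Gender is likely to explain a noticeable share of the variance in body weight and waist. The trial plans for 96 evaluable participants, about 32 per arm, so there is little precision to spare. The main comparison of interest, Facebook against pamphlet, is reached only after a significant between-groups result. A conservative test at that step can therefore stop the comparison from being made at all.

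**Working it through.** **Inputs from the document**
- Evaluable sample: "a sample size of 96 achieves 80 % statistical power to detect a medium to large effect size". Per arm: 96/3 = 32.
- Effect and alpha: "a difference of 6 kg between the two intervention groups, with alpha set at 0.05". With the stated d of 0.4, the implied SD is 6/0.4 = 15 kg.
- Recruitment: "To allow for an attrition rate of 20 %, a total of 120 participants will be recruited; i.e. 40 participants per group". Check: 96/(1 − 0.20) = 120 and 120/3 = 40, so the inflation reproduces. The 96 itself cannot be reproduced from the stated inputs alone. That is a separate matter and does not affect this point.

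**Assumed, not in the document:** R², the share of outcome variance explained by age and gender. For weight level, suppose 35% men and a gender gap of 10 to 14 kg. Gender alone then explains gap² × p(1 − p)/SD²:
- 10 kg: 100 × 0.35 × 0.65/225 = 0.10
- 14 kg: 196 × 0.35 × 0.65/225 = 0.20

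Higher values (0.30, 0.40) are shown to complete the range. For weight change, 0.02 to 0.10 is assumed.

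**Formulas.** With the arms balanced on the strata, the true standard error reflects only the residual variance, while the model without the factors reports the total variance:
- reported SE / true SE = 1/√(1 − R²)
- actual two-sided type I error = 2 × [1 − Φ(1.96/√(1 − R²))]
- power without the factors, where the model with them has 80% = Φ(2.80 − 1.96/√(1 − R²)), since 1.96 + 0.84 = 2.80

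| R² | SE too large by | Actual type I error at nominal 5% | Power where the adjusted test has 80% |
|---|---|---|---|
| 0.02 | 1% | 4.8% | 79% |
| 0.05 | 3% | 4.4% | 79% |
| 0.10 | 5% | 3.9% | 77% |
| 0.20 | 12% | 2.8% | 73% |
| 0.30 | 20% | 1.9% | 68% |
| 0.40 | 29% | 1.1% | 61% |

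**Which rows apply to which test**
- *Weight change or group-by-time.* Subtracting one visit from another removes each person's stable level, including the stable part of age and gender differences. Only effects of age or gender on change remain in the error. The rows from 0.02 to 0.10 apply.
- *Between-groups effect on level.* This is tested against between-person variance, where gender differences in weight and waist sit. The rows from 0.10 upwards apply.

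**Simulation check.** 4,000 runs, N = 96, three arms, four strata, blocks of 6, using the three-arm F test (so figures differ slightly from the single-contrast formula).

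| Test | R² | Type I error, without / with strata | Power at 0.6 SD, without / with strata |
|---|---|---|---|
| Level | 0.20 | 2.4% / 4.7% | 70% / 80% |
| Level | 0.30 | 1.5% / 5.4% | 69% / 84% |
| Level | 0.40 | 0.9% / 5.0% | 69% / 89% |
| Change | 0.02 | 5.0% / 5.3% | 69.5% / 70.3% |
| Change | 0.05 | 4.8% / 5.7% | 68.9% / 71.2% |
| Change | 0.10 | 3.6% / 4.6% | 69.0% / 73.5% |

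The simulation agrees with the formulas in direction and rough size. The loss is small for change and material for level.

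**The case against.** The strongest objection is that the article is silent rather than wrong. It names a class of model and lists no terms, and a condensed article may leave covariates to a full protocol or analysis plan that is not shown. This stands against one inference a reader might draw, that the trial has decided to ignore age and gender. The document does not support that. It does not remove the point: the article names the model, the condition for pairwise tests, the post hoc method, alpha and the software, and mentions the stratifiers in the same paragraph only as a means of matching the groups.

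The second objection is about size. Outcome measures and Hypotheses frame the main question as weight loss, and in a repeated measures design that is the group-by-time contrast, where stable gender and age differences already drop out. This stands, and it limits the loss there to about 1 to 5% of the standard error under the assumed R². The larger figures need the conditional step to mean the between-groups main effect. That is the literal reading, but the wording could be looser. If the main effect is meant, whether it is the right term to test for weight loss is a further question that adding covariates would not settle.

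A reader might also infer that wrongly sized standard errors make the trial's positive findings unsafe. The opposite holds: the error is on the cautious side.

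**Conclusion.** The point holds in a limited form. The model as described carries neither stratification factor. Run that way, it overstates between-arm standard errors and gives conservative tests, without bias and without extra false positives.

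Under the assumed R², the excess is about 1 to 5% for weight change or group-by-time, and about 5 to 12% or more for the between-groups effect on weight or waist level. In the level case, a comparison that would have 80% power with adjustment has about 77% at R² 0.10 and 73% at R² 0.20.

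These figures rest on values of R² that the article does not supply, and on allocation that actually balances the arms within strata, as the article intends. Dropout that disturbs the balance would shrink the excess. This is an inexpensive improvement to the plan. It does not show that the analysis is invalid.

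**What to change.** State in the analysis section that gender and age (as the stratum or as continuous age) are covariates in the between-arm models, in one of two forms:

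- If the repeated measures ANOVA is kept, add covariate-by-time terms. Main effects alone leave a complete-data group-by-time contrast essentially unchanged.
- Otherwise, enter the baseline value as a covariate with gender and age, and take week 0 out of the repeated outcomes.

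If an unseen analysis plan already does this, only the article's description needs to be aligned.

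The cost is a few degrees of freedom. With 96 participants in three arms there are 96 − 3 = 93 for between-person error; gender plus continuous age as a linear term uses 2. Full strata with k age bands use 2k − 1, so 3 for two bands and 5 for three. The actual number cannot be given because the bands are not stated. The second form is more than a wording change, since it turns the analysis into a baseline-adjusted one, but it needs no new data.
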